### 2.10 Data management

Research data will be managed through an electronic case report form (eCRF). In the development of the eCRF, range checks for data values will be implemented for each parameter to minimize the possibility of errors. Investigators will enter study data into the eCRF, and Clinical Research Associates (CRAs) will perform full Source Data Verification (SDV) through regular monitoring of all entered data. Data lock will be executed once verification of all data is completed and preparations for statistical analysis are finalized, including the completion of blind data review meetings for analysis group determination.

### 2.11 Statistical methods

#### 2.11.1 Analysis set

Efficacy data will be primarily analyzed using the Per-Protocol (PP) set, with additional analyses conducted on the Intent-to-Treat (ITT) and Full Analysis (FA) sets. Safety data will be analyzed using the Safety Analysis (SA) set.

The ITT set will include all participants enrolled in this clinical trial. The SA set will comprise subjects who consumed the investigational product at least once after enrollment. The FA set will include all randomized participants with at least one efficacy evaluation after consuming the investigational product. Participants who violated inclusion/exclusion criteria or never consumed the investigational product will be excluded from the FA set. The PP set will consist of participants from the FA set who completed the trial according to the protocol without major violations. Participants who used prohibited concomitant medications or committed other serious protocol violations will be excluded from the PP set. Other serious protocol violations will be determined through a blind data review meeting.

Statistical analyses will be performed using SAS for Windows, with statistical significance set at *p* < 0.05. Missing values will be replaced using the Last Observation Carried Forward (LOCF) method. Baseline characteristics between groups will be compared using Chi-Square test or Fisher’s exact test for categorical variables and Independent *t*-test for continuous variables.

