Meanwhile, recent research has suggested the potential anti-fatigue effects of *Pinus koraiensis* leaf extract (PKL). According to a single animal study by Lee et al. (9), PKL extract improved exercise endurance in mice during weight-loaded forced swimming and rotarod tests. In terms of biochemical markers, PKL extract significantly reduced blood lactate and LDH levels related to anaerobic metabolism, as well as decreased CK levels, an indicator of muscle damage. Regarding aerobic metabolism, PKL extract significantly increased the levels of antioxidant enzymes SOD and GSH-Px, which typically decrease after exercise, demonstrating a protective effect against oxidative stress. Additionally, PKL extract improved energy metabolism by increasing glycogen levels in both liver and muscle. These results suggest that PKL extract may exert anti-fatigue effects through metabolic regulation, and antioxidant activity. Based on these promising animal findings, whether these effects also occur in humans has not yet been explored.

Therefore, this study was designed to evaluate whether the anti-fatigue effects of PKL extract observed in previous animal experiments also occur in humans. Specifically, we aim to assess the anti-fatigue and exercise performance-enhancing effects of 8-weeks PKL extract consumption compared to placebo intake in healthy adults with high fatigue levels. If the efficacy of PKL extract in humans is confirmed through this study, it could be developed as a new functional food ingredient for fatigue improvement. This clinical trial was designed as a randomized controlled trial comparing the superiority of the PKL extract group over the placebo group, with parallel comparison between the two groups, and an allocation ratio of 1:1.

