### 2.6 Sample size

The sample size of this clinical trial is 50 participants per group. Although no preliminary data on PKL extract’s anti-fatigue effects in humans are available, we referenced a study using fermented porcine placental (FPP) extract (26), which has received Korean MFDS approval for fatigue improvement, as PKL extract is pursuing the same regulatory pathway. In that study, the FPP group (*n* = 36) showed a mean change in FSS score of −9.79, while the placebo group (*n* = 31) demonstrated a mean change of −5.20. Based on the reference study data showing a mean difference of 4.59 points in FSS score change between treatment and placebo groups, and assuming a pooled standard deviation of 6.8, we calculated the required sample size. With a significance level of 0.05 and a power of 0.8 for a two-sided test, we estimated that a minimum of 35 participants per group would be required. Considering an anticipated dropout rate of approximately 30% during the clinical trial process, we decided to recruit a total of 100 participants, with 50 participants per group.

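### A superiority trial makes the per-protocol set its primary efficacy population, so the main test is not protected by randomisation

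*Protocol article*

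**What the plan says.** The Introduction describes the trial as "randomized controlled trial comparing the superiority of the PKL extract group over the placebo group", with "an allocation ratio of 1:1".

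Section 2.11.1 sets the order of the efficacy populations: "Efficacy data will be primarily analyzed using the Per-Protocol (PP) set". The ITT and FA sets serve only for further analyses. It builds the PP set in two steps:
- First, by completion and conduct: "The PP set will consist of participants from the FA set who completed the trial according to the protocol without major violations".
- Second, by removing anyone who took a prohibited medication or broke the protocol seriously in some other way. The other serious violations are settled at a blind data review meeting.

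The same section defines the ITT set as everyone enrolled and fills missing values by LOCF. Section 2.6 plans for loss: "Considering an anticipated dropout rate of approximately 30% during the clinical trial process", 50 per group are recruited so that 35 remain. The article gives no reason for putting PP first.

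**The concern.** Randomisation makes the two groups comparable as allocated. A population chosen by what happened afterwards does not inherit that comparability unless the selection is unrelated to treatment and outcome, and little here suggests that it would be. Section 2.3.2 lists adverse events, difficulty consuming the product, withdrawn consent, loss to follow-up and prohibited medication among the reasons for ending participation. Section 2.3.4 withdraws participants who take a medication or health functional food that could affect the efficacy evaluation, and it bars other fatigue remedies. Tolerability can differ between extract and placebo, and a participant who is still tired has more reason to try another remedy.

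At stake is the headline result. If the PP analysis were significant and the ITT analysis were not, the plan as written would treat PP as the main finding. Section 4.5 sends the results to the regulator.

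**Working it through.** **1. Inputs (section 2.6).** Difference in FSS change 4.59; SD 6.8 (assumed there); two-sided alpha 0.05; power 0.80; dropout about 30%; 35 evaluable and 50 recruited per group.

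**2. The plan's own figures.** n = 2 × [(1.960 + 0.842) × 6.8 / 4.59]² = 34.45, so 35 per group (a t-based calculation gives 35.44, so 36). Inflation: 35 / 0.70 = 50. The figures reproduce. At the planned dropout the primary test uses 2 × 35 = 70 of 100 randomised, with power of 81% (79% by t-test).

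**3. When each exclusion is determined.** Eligibility violations, removed at the FA step, rest on facts that precede randomisation. Completion, use of prohibited products and other violations of conduct come after it.

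**4. Possible size of the bias.** The documents give no exclusion rate by arm and no link between exclusion and outcome, so these are assumptions: no true effect; 30% excluded in each arm; exclusion correlated (ρ) with FSS change in one arm only; SD held at 6.8.
- Shift in the mean of those retained = ρ × 6.8 × φ(z₀.₃) / 0.7, with φ(z₀.₃) = 0.3477.
- ρ = 0: no shift, type I error 5%.
- ρ = 0.3: 0.3 × 6.8 × 0.3477 / 0.7 = 1.01 points, or 22% of 4.59.
- ρ = 0.5: 0.5 × 6.8 × 0.3477 / 0.7 = 1.69 points, or 37% of 4.59.
- SE = 6.8 × √(2/35) = 1.63.
- Type I error = P(|Z + shift/SE| > 1.96) = 9.6% for ρ = 0.3 and 18.0% for ρ = 0.5.

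The sign depends on the arm. Losing poor responders from the PKL arm alone favours the product; losing them from the placebo arm alone shifts the difference by the same amount against it. Equal selection in both arms cancels.

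**5. A second model.** Suppose the excluded 30% of one arm would have done D points worse than that arm's completers. The bias is 0.3 × D. For D = 2, 4 and 6 this is 0.6, 1.2 and 1.8 points, with rejection rates of about 7%, 11% and 20%. The order of magnitude agrees.

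**6. Power if all randomised participants are primary.** Let the 30% who discontinue retain a fraction f of the effect (assumed range). Then δ = 4.59 × (0.7 + 0.3f), SE = 6.8 × √(2/50) = 1.36, and power = Φ(δ/1.36 − 1.96).

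| f | δ | Power, 50 per group | n per group for 80% |
|---|---|---|---|
| 1 | 4.59 | 92% | 35 |
| 0.75 | 4.25 | 88% | 41 |
| 0.5 | 3.90 | 82% | 48 |
| 0.25 | 3.56 | 74% | 58 |
| 0 | 3.21 | 66% | 71 |

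These powers count 50 informative outcomes per group. Missing 8-week values would lower them.

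**The case against.** **Safeguards exist.** The trial is double-blind, set membership is settled at a blind review before data lock, and ITT and FA analyses are prespecified, so a discrepancy between sets would be visible. This stands as mitigation: it limits deliberate selection, and a randomised comparison is still present in the plan. It does not make completion independent of treatment, and it does not change which analysis is the main one. The Discussion says that the trial follows the regulator's functional evaluation guidelines, but not that these call for a PP primary analysis.

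**Much of the bias is a dropout problem.** Most who leave will have no 8-week value whichever set is primary. Treadmill time is measured only at baseline and 8 weeks, so a dropout has no post-baseline value at all. This stands. The loss due strictly to choosing PP is the discarding of observed data from violators, for which the documents give no rate. A reader might infer that naming ITT primary would remove the whole bias in step 4. It would not; the handling of missing data must change as well.

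**Direction.** A reader might infer that a completer set favours the product. The documents do not support that. If lack of benefit drives people out or towards other remedies, poor responders may leave the placebo arm more often, which flatters placebo.

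**The 30%.** A reader might take it as the most that PP can drop. It is an anticipated dropout rate: violations among completers would add to it, and actual dropout may be lower.

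**Conclusion.** The concern holds for the stated ordering: a superiority trial puts PP ahead of ITT and FA without giving a reason, and the primary test then conditions on events that largely follow randomisation. This is a rule that the article fixes itself, not a detail left to an analysis plan, and it governs the confirmatory test.

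The size is uncertain. Under the assumed one-arm selection, the shift is about 1.0 to 1.7 FSS points in either direction, with type I error of about 10% to 18%; with equal selection there is none. The correlations of 0.3 and 0.5 and the one-arm pattern have no source in the documents. The figures show what the design leaves open, not what will happen.

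**What to change.** Before unblinding, change section 2.11.1 as follows:
- Define ITT as all randomised participants, analysed as randomised. The present definition refers to those enrolled, and section 2.8 describes enrolled participants as then being assigned randomisation numbers.
- Make ITT primary for FSS and treadmill time, with FA and PP supportive.
- Use every observed 8-week value, including those from protocol violators.
- Replace LOCF in the primary analysis with a likelihood-based or multiple-imputation method, and add a sensitivity analysis for informative dropout. LOCF would set the treadmill change of every dropout to zero.

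**Cost.** This takes more than one sentence, because the set order, the ITT definition and the missing-data rule all change. The estimate may be less favourable than among completers. The planned 100 participants keep the stated 80% power only if discontinuers retain about half the effect or more; at a quarter or none, 58 or 71 per group would be needed. The protocol should state that assumption beside the sample size.

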### 2.4 Outcomes

#### 2.4.1 Primary outcomes

The Fatigue Severity Scale (FSS) scores change from baseline to 8 weeks is designated as the first primary outcome (17, 18). The FSS is a self-administered questionnaire consisting of 9 items that evaluate the subjective level of fatigue-related disability on a scale of 1–7. Scores below 27 indicate “low fatigue,” scores between 27 and 44 indicate “medium fatigue,” and scores of 45 or above indicate “high fatigue.” FSS will be measured at baseline, 4 weeks, and 8 weeks.

The second primary outcome is the change in time and distance to exhaustion during a treadmill exercise test from baseline to 8 weeks. The exercise test utilizes the Modified Bruce protocol, which progressively increases both speed and incline to measure exercise capacity (19). The test begins at stage 1 (2.7 km/h, 0% grade, 3 min) and continues through predefined stages of increasing difficulty (stage 2: 2.7 km/h, 5% grade, 3 min; stage 3: 2.7 km/h, 10% grade, 3 min; stage 4: 4.0 km/h, 12% grade, 3 min; stage 5: 5.4 km/h, 14% grade, 3 min; stage 6: 6.7 km/h, 16% grade, 3 min; stage 7: 8.0 km/h, 18% grade, 3 min). The test is terminated when the participant voluntarily requests to stop. The distance to exhaustion is calculated using the total exercise duration and speed. Treadmill exercise test will be conducted at baseline, and 8 weeks.

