#### 2.11.2 Statistical methods for analyzing efficacy outcomes

For primary and secondary efficacy endpoints, descriptive statistics will be presented by treatment group, and comparisons will be made both between groups.

For between-group comparisons, changes from baseline (post-8-weeks consumption minus pre-consumption) will be analyzed using independent *t*-test if normality assumptions are met, or Mann-Whitney U test if not. The proportion of participants showing improvement in efficacy variables at 8 weeks compared to baseline may be analyzed using Chi-Square test or Fisher’s exact test.

For repeated measurements of FSS (excluding the primary efficacy endpoint analysis), VAS for subjective fatigue, and grip strength (measured three times), RM-ANOVA or Linear Mixed Model will be used for between-group comparisons if normality assumptions are met or appropriate non-parametric methods if not. In cases of severe violation of normality assumptions, variable transformation methods such as logarithm transformation may be applied before analysis.

Additionally, ANCOVA or ranked ANCOVA may be performed with covariates including lifestyle factors (dietary intake, physical activity, alcohol consumption, smoking, occupation, etc.), baseline values and changes in lifestyle factors, baseline values of efficacy variables that are not homogeneous between groups, and demographic information.

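### Last observation carried forward gives every treadmill dropout a change of exactly zero and biases the ITT and FA analyses in a direction that the protocol does not allow one to predict

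*Protocol article*

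**What the plan says.** Section 2.11.1 states: "Missing values will be replaced using the Last Observation Carried Forward (LOCF) method". The rule is not limited to any endpoint or analysis set, and the article names no alternative method.

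The visit schedule in section 2.4.1 decides what can be carried. For the second primary outcome: "Treadmill exercise test will be conducted at baseline, and 8 weeks". For the first: "FSS will be measured at baseline, 4 weeks, and 8 weeks". Section 2.4.2 places the blood fatigue markers at baseline and week 8 only. Section 2.11.2 compares the arms on week 8 minus baseline, by t-test or Mann-Whitney test.

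On the analysis sets, section 2.11.1 says: "Efficacy data will be primarily analyzed using the Per-Protocol (PP) set, with additional analyses conducted on the Intent-to-Treat (ITT) and Full Analysis (FA) sets". The sets are defined as follows:
- ITT: "The ITT set will include all participants enrolled in this clinical trial".
- FA: "The FA set will include all randomized participants with at least one efficacy evaluation after consuming the investigational product".
- PP: "The PP set will consist of participants from the FA set who completed the trial according to the protocol without major violations".

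Section 2.11.2 names a linear mixed model as an option, but with a carve-out: "For repeated measurements of FSS (excluding the primary efficacy endpoint analysis"). Section 2.6 allows for about 30% dropout and does not split it by arm.

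**The concern.** LOCF enters a guessed value as if it had been measured. With no treadmill test between baseline and week 8, the guess is the participant's own baseline, so the change score is zero by construction. For FSS the score is frozen at week 4 or at baseline, although the planning figures in section 2.6 have both arms improving (−9.79 and −5.20).

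Two things are at stake. First, the estimated difference moves away from the true one by an amount set by who drops out and when. Second, the test counts the imputed participants as fully observed, so its standard error does not reflect the lost information. The results are intended for a regulatory submission (section 4.5). The ITT and FA analyses are the ones a reader would use to check whether the completer-based primary result depends on who completed.

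**Working it through.** **Inputs from section 2.6.** Mean FSS change −9.79 (active) and −5.20 (placebo), difference 4.59, SD 6.8, two-sided 5% level, power 80%, 35 evaluable and 50 randomised per arm, about 30% dropout.

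**The plan's own figure.** n per arm = 2 × [6.8 × (1.960 + 0.842) / 4.59]² = 34.45, rounded up to 35. Then 35 / (1 − 0.30) = 50. Both figures reproduce. With 50 complete per arm, SE = 6.8 × √(2/50) = 1.36, and power = Φ(4.59/1.36 − 1.96) = 92%.

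**Assumptions not in the documents.** Dropout by arm (d); dropouts would have had the same mean change as completers; and f, the share of the final mean change already present in the carried value. Baseline carried forward is f = 0. For week-4 carry, f = 0.5 is used as an illustration.

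**Formula.** With m the true mean improvement in an arm, the LOCF mean is m × [1 − d(1 − f)].

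**True difference 4.59:**

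| Dropout PKL / placebo | LOCF difference, f = 0 | LOCF difference, f = 0.5 |
|---|---|---|
| 10% / 10% | 0.9 × 4.59 = 4.13 | 0.95 × 4.59 = 4.36 |
| 20% / 20% | 0.8 × 4.59 = 3.67 | 0.9 × 4.59 = 4.13 |
| 30% / 30% | 6.853 − 3.640 = 3.21 | 8.321 − 4.420 = 3.90 |
| 40% / 20% | 5.874 − 4.160 = 1.71 | 7.832 − 4.680 = 3.15 |
| 20% / 40% | 7.832 − 3.120 = 4.71 | 8.811 − 4.160 = 4.65 |

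The bias changes sign where d(PKL) × 9.79 = d(placebo) × 5.20. LOCF therefore overstates the effect once placebo dropout exceeds 9.79/5.20 = 1.88 times PKL dropout.

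**Standard error and power, f = 0, 30% / 30%.** The variance of change in an arm is (1 − d) × 6.8² + d(1 − d) × m².
- PKL: 0.7 × 46.24 + 0.21 × 95.84 = 52.5.
- Placebo: 0.7 × 46.24 + 0.21 × 27.04 = 38.0.
- SE = √[(52.5 + 38.0)/50] = 1.35, and power = Φ(3.21/1.35 − 1.96), about 67%.

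This SE is about that of 50 complete participants per arm (1.36), although only 35 per arm were observed: 6.8 × √(2/35) = 1.63.

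**No true effect (both arms improve by 5.20), f = 0, 20% / 40%.**
- LOCF difference: 0.8 × 5.20 − 0.6 × 5.20 = 1.04 in favour of PKL.
- Variances: 0.8 × 46.24 + 0.16 × 27.04 = 41.3, and 0.6 × 46.24 + 0.24 × 27.04 = 34.2.
- SE = √[(41.3 + 34.2)/50] = 1.23.
- Chance of significance in favour of PKL = Φ(1.04/1.23 − 1.96), about 13%, against a nominal 2.5%. At 25% / 35% it is about 6%; at 30% / 30% it stays at 2.5%.

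**Treadmill.** The protocol gives no treadmill means or SD, so only a proportion can be stated. With equal dropout of 30%, the difference is 0.7 × δ + 0.3 × 0 = 0.7δ, on the same assumption about dropouts.

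**The case against.** The strongest point against the concern is that the primary efficacy set is per-protocol. Completers leave LOCF little to fill in, so the headline analysis is barely touched. That stands, and a reader who infers that LOCF distorts the primary result goes further than the documents allow. Restricting the primary analysis to completers raises its own question, but a separate one.

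A reader might also infer that LOCF simply understates the effect and is therefore conservative. The protocol does not support that. Understatement follows if dropout is equal and both arms improve, but the article gives neither dropout by arm nor the time course, and the table shows overstatement at 20% / 40%.

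Nor does baseline carry of FSS apply equally to both sets. FA membership requires an efficacy evaluation after dosing, so an FA dropout would normally carry the week-4 FSS. Baseline carry is mainly an ITT matter. The treadmill zeros arise in both sets, because a participant with only a week-4 FSS qualifies for FA.

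Three further points are fair. The 30% is a planning allowance, and at 10% in both arms the shrinkage is modest. If dropouts really did return to baseline, the carried baseline would be about right on average; the protocol does not argue this, and the imputed values would still be counted as observed. Finally, likelihood methods and multiple imputation rest on an untestable assumption of their own, which is why a sensitivity analysis belongs with them.

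An unseen analysis plan does not answer the point: LOCF is written into the protocol without qualification.

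**Conclusion.** The concern holds for the ITT and FA analyses. It is certain from the schedule that LOCF assigns zero change to each participant in those sets who has a baseline treadmill test but no week-8 test, and that a missing week-8 FSS is frozen at an earlier value. Bias in the estimates and in their standard errors follows unless dropouts happen to stay where they were last seen.

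The direction cannot be fixed in advance. Using the FSS planning figures with baseline carried forward, a true 4.59 could appear as anything from about 1.7 to 4.7 across the unequal dropout splits shown, and a null effect could appear as a benefit of about 1.0 point. These sizes rest on assumed dropout by arm and on dropouts sharing the completers' mean change. Week-4 carry with f = 0.5 gives smaller errors (3.15 to 4.65).

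This should be fixed, but it does not invalidate the primary analysis. It matters because ITT and FA are the checks on the selection built into the per-protocol set, and LOCF undermines those checks.

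**What to change.** Delete the LOCF rule for efficacy outcomes and, for the ITT and FA analyses, state instead:

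- **FSS:** the linear mixed model that section 2.11.2 already names, fitted to the week-4 and week-8 values with adjustment for baseline, reporting the week-8 contrast between arms. Remove the carve-out that keeps this model away from the primary endpoint in these two sets.
- **Treadmill time and distance:** ANCOVA after multiple imputation, with arm, baseline treadmill value and the FSS values in the imputation model. The blood markers, which share the two-visit schedule, can be handled in the same way.
- **Sensitivity:** one analysis for data not missing at random, such as imputing dropouts by reference to the placebo arm.

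The cost is a change of wording and a little more SAS programming, with no new data, and it can be made before unblinding. The change leaves the per-protocol set as the primary set; whether it should remain so is a separate question.
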